### Healthcare use

Healthcare use will be measured by items derived from the iMTA Medical Consumption Questionnaire [48]. Healthcare use, as well as patient and family costs will be measured, including: 1) the number of appointments with a general practitioner, practice nurse, physiotherapist, occupational therapist, speech therapist or dietician, 2) hospital care, i.e. acute care, outpatient care or admissions, 3) informal care, and 4) medication use. The valuation of all costs is based on the updated Dutch manual for cost analyses in healthcare research, of which an updated version of 2021 will be used to express current cost-prices [49]. A schematic overview of the enrolment, interventions and assessments, according to the SPIRIT 2013 guidelines, is presented in Table 2 [41].

**Table 2 Tab2:** Schematic overview of enrolment, interventions and assessments

	**STUDY PERIOD**				
	**Enrolment**	**Allocation**	**Post-allocation**		**Close-out **^**a**^
**TIMEPOINT**	***-t***_***1***_	**0**	***t***_***0***_	***t***_***1***_	***t***_***2***_
**ENROLMENT:**					
**Eligibility screen**	X				
**Informed consent**	X				
**Allocation**		X			
**INTERVENTIONS:**					
***SELF-program***			X		
***Care as usual***			X	X	X
**ASSESSMENTS:**					
**Nurses:**					
*** Demographic variables***		X			
*** MAINtAIN questionnaire***		X		X	X
**ASSESSMENTS:**					
**Geriatric clients:**					
*** Demographic variables***		X			
*** GARS-4 questionnaire***		X		X	X
*** EQ-5D-5L questionnaire***		X		X	X
*** Economic evaluation variables***		X		X	X

^a^9 months for nursing care professionals and 6 months for geriatric clients respectively

### Process evaluation

Parallel to the effect and economic evaluation, a comprehensive process evaluation will be performed according to the guidelines of the MRC-framework [50]. The process evaluation intends to assess the feasibility of the SELF-program regarding implementation, its mechanisms of impact and contextual factors that potentially have an influence on implementation and outcomes. Process evaluations of complex interventions usually consist of mixed-method approaches, including both qualitative and quantitative data-collection methods (focus group) interviews and questionnaires. This study applies both methods among program participants and those delivering the program, i.e. trainers.

### Implementation

Effects of an intervention may depend on the degree to which the intervention was implemented [50]. Commonly, process evaluations investigate a number of implementation parameters to draw reliable conclusions about a program’s effectiveness, including fidelity (whether the intervention was delivered according to plan), dose delivered (quantity of the intervention delivered), dose satisfaction (quantitative and qualitative evaluation of satisfaction with the intervention), adaptations (adaptations made to the intervention during implementation), and reach (whether and to what extent the intended target audience is exposed to the intervention). Data on implementation will be collected from various sources, through different data-collection methods, i.e. questionnaires, (attendance) logbooks, focus group interviews, and checklists, and on various time points of which before, during and after implementation (see Table 3).

**Table 3 Tab3:** Overview of data collection for process evaluation

Process evaluation component	Source	Data-collection method	Time points
**Implementation**			
*Fidelity*			
Delivery according to plan	Trainers	Checklists and focus group interviews	During and after implementation
*Dose delivered*			
Quantity of delivery	Trainers	Checklists and focus group interviews	During and after implementation
*Dose satisfaction*			
Satisfaction intervention (delivery)	Interventionists	Questionnaire and focus group interviews	During and after implementation
*Adaptations*			
Alterations made during implementation	Trainers	Logbook and focus group interviews	During and after implementation
*Reach*			
Extent to which target group was exposed to intervention	Interventionists	Attendance logbook and focus group interviews	During and after implementation
**Mechanisms of impact**			
Mechanisms assumed to produce change in outcome behavior	Interventionists	Questionnaire (31 items) Focus groupinterviews	Baseline, 3 months and 9 months after baseline
**Contextual factors**			
Barriers and facilitating factors that may influence implementation and outcomes	Trainers and Interventionists	Logbook and focus group interviews	During and after implementation

### Mechanisms of impact

An exploration of the mechanisms through which interventions impact the desired behavior change is pivotal to understand how such effects occurred [51]. The primary outcome of the SELF-program is the level of stimulation behavior of self-reliance in activities of daily living among geriatric clients. In its core, the Integrated Change Model, applied as theoretical background to the SELF-program, assumes that a particular behavior is predicted from personal beliefs related to ones attitudes, perceptions of social influence, perceived self-efficacy in challenging situations, and intention [32]. A total of 31 mechanisms of impact questions will be addressed: attitudes will be measured with 11 items, perceptions of social influence with 8 items, and intention with a single item, which all can be rated on a 5-point Likert scale ranging from ‘totally disagree’ to ‘totally agree’. Self-efficacy will be measured with 11 items that can be rated on a 5-point Likert scale, ranging from ‘no confidence’ to ‘total confidence. Items are derived from previous work on beliefs of stimulation behavior, and previous applications of the Integrated Change Model [32, 52].

### Contextual factors

External factors may act as a barrier or facilitating factor to the implementation of an intervention and its outcomes [50]. Understanding the context in which an intervention is implemented is important to interpret findings and generalize results beyond it. Therefore, a logbook will be kept on those factors acting as barriers or facilitators to the implementation and outcomes of the SELF-program. In addition, post-implementation focus group interviews with interventionists and trainers will discuss relevant contextual factors and suggestions for improving the SELF-program. Table 3 presents an overview of the data-collection of the process-evaluation.

### Data analyses

#### Effect evaluation

Summary statistics of central tendency (mean, median) and dispersion (standard deviation, interquartile range) will be used for continuous variables, as appropriate, to describe the two groups, whereas categorical variables will be summarized by absolute count and relative percentages (%).

Effect evaluation will be conducted according to the intention-to-treat principle with mixed (multilevel) linear regression analyses to accommodate the hierarchical structure of the data: measurements are nested within individuals, which are nested within a ward. Both wards and subjects will constitute the random effects (three-level models). Treatment, time and, their interaction, capturing treatment vs. control average differences over time, will make up the relevant fixed-effects, together with background characteristics that will be included in the model as covariates. Outcomes will be standardized to be interpreted as effect sizes (Cohen’s *d*). The regression coefficient of the treatment*time interaction in the mixed linear regression analysis can, therefore, be interpreted as Cohen’s *d*. To establish which factors are linked to (a possible) differential attrition between the groups, a logistic regression analysis with be conducted. SPSS for Windows, version 27 will be used for all statistical analyses. The level of statistical significance will be set at 0.05 (using two-tailed tests). In case of significant interactions, subgroup analyses will be conducted to determine the differential effects. In case of unintended effects due to the intervention or due to the trial conduct, these will be reported accordingly.

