### Procedure and recruitment of participants

To examine the program’s effectiveness and cost-effectiveness, two participant groups will be recruited, i.e., nurses working in nursing home care and geriatric clients receiving nursing home care. Care organizations across the Netherlands are able to take part in the study as the SELF-program is widely disseminated through various (social) media platforms and national conferences. To be eligible to participate, organizations have to offer nursing home care. In case of organizational willingness to participate, formal approval of the board of directors will be requested and the client council will be informed about the study. In close agreement with organizational boards and team and location managers, nursing home wards will be selected to participate in the trial. Wards hosting somatic clients, as well as wards where psychogeriatric clients reside are eligible to be included in the study. Within an organization, dyads will be created consisting of two nursing home wards, which will then be pair-matched according to size and ward type, e.g., somatic or psychogeriatric ward. Of the two included wards from a dyad, one will be randomly allocated into the intervention group (SELF-program) or into the control group (care as usual), and clients residing at a ward will be allocated accordingly. Randomization will be conducted by means of computer-randomization using *random.org.* The unit of intervention will be the care ward, the unit of analysis will be the nursing care professional or the resident respectively.

To minimize the probability of contamination bias, dyads will be created of wards that do not collaborate in daily practice. In case of collaboration between wards, something likely to occur within nursing homes, randomization will take place on location level. Nursing home organizations in the Netherlands usually consist of multiple locations, which in turn consist of a varying number of wards. In the event of collaboration between wards within a location, the entire location is included in a dyad with a pair-matched comparator location. For example, a nursing home location with three collaborating psychogeriatric wards, will be pair-matched with a similar location.

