### Geriatric clients

Geriatric clients are eligible to participate if they are residing at the concerned ward at time of ward inclusion. Clients are excluded from participation when aged < 65 years old, or when terminally ill or bedbound. In addition, those with a temporary stay (< 6 months) are excluded. Data collection for geriatric clients will be accomplished by the primary responsible caregiver, who will be asked to fill in the questionnaires for their client(s). Depending on the level of cognitive and physical impairment, the primary responsible caregiver can fill in the questionnaire alone or together with the geriatric client. Before data-collection of geriatric clients, written informed consent will be obtained from either the client itself or a responsible party, generally a family member appointed as the primary contact person of the client.

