### Sample size calculation

Given the cluster-randomized trial design, the guidelines prescribed by Breukelen and Candel (2012) were applied for sample size calculation (N) [44]. The SELF-program is expected to induce a difference in groups’ averages of the primary outcome (the MAINtAIN-score), corresponding to a small to medium effect size of 0.4 (Cohen’s *d*). Further, the mean cluster size, i.e. the average number of nursing care professionals per ward, is estimated to be 15. Using the two-tailed t-test, with power and significance level of 80% and 5%, respectively, the required number of clusters (K) was then computed, using an interclass correlation coefficient of 0.05 to correct for the cluster-randomized design effect (DE), yielding K ~ 8. Subsequently, K was increased in 10% to adjust for differences cluster sizes, and the associated sample size was further augmented to account for a 20% attrition of care professionals between baseline and post-treatment. This yielded a total sample size of *N* = 330 (165 per arm) care professionals and geriatric clients in K = 22 nursing home wards, or 11 ‘dyads’. In order to achieve adequate participant enrolment, we aim to include > 22 nursing home wards.

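### The effect model names only ward and subject random effects, so errors shared by a caregiver's clients or by a ward that change between waves can inflate the treatment-by-time test

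*Protocol article*

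**What the plan says.** Client data come from proxies. Under Geriatric clients (recruitment), collection is done by "the primary responsible caregiver, who will be asked to fill in the questionnaires for their client(s"), alone or together with the client. The Discussion confirms that this applies to somatic clients too. The number of clients per caregiver is not given.

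Under Data analyses, Effect evaluation, the structure is that "measurements are nested within individuals, which are nested within a ward", and "Both wards and subjects will constitute the random effects (three-level models"). The same section describes the effect of interest as the treatment-by-time coefficient: "The regression coefficient of the treatment*time interaction in the mixed linear regression analysis can, therefore, be interpreted as Cohen’s" *d*. On error control: "The level of statistical significance will be set at 0.05 (using two-tailed tests").

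Allocation is by ward within dyads, or by location where wards collaborate: "Of the two included wards from a dyad, one will be randomly allocated into the intervention group (SELF-program") and the other to usual care. Sample size calculation gives the same N = 330 in 22 wards for care professionals and for clients. It also enlarges the sample to "account for a 20% attrition of care professionals between baseline and post-treatment".

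Under Data analyses, Economic evaluation, costs and QALYs over 6 months are regressed per client. Clustering is handled by random intercepts, but only if judged necessary.

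**The concern.** Clients scored by the same caregiver share that person's scoring habit. A habit that moves between waves, or a change of rater, shifts the change scores of all those clients together. Neither a client intercept nor a ward intercept represents this, because both are constant over time. The shared movement goes into the residual and is counted as independent information for each client.

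The protocol makes such movement plausible. The raters belong to the staff whose awareness and attitudes the programme sets out to change between T0 and T1, and the GARS-4 records perceived self-reliance. Some raters may leave. The same reasoning applies one level up: the training is delivered to a whole team and tailored to it, so wards can move over time as units.

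At stake is the 5% error rate of the treatment-by-time test for the main client outcome. For ward-level movement, the nurse primary outcome is exposed as well.

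**Working it through.** **Inputs from the protocol:** 22 wards (11 per arm), about 15 persons per ward (estimated for nurses, with the same total of 330 given for clients), three waves, two-sided 5%. This gives n = 11 × 15 = 165 clients per arm.

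**Assumed, because the protocol gives no values:** clients per caregiver m = 1, 3 or 5; variance components as shares of a total of 1.

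**The plan's own figure.** The only one that bears on this point is the nominal 5%. With no caregiver error, simulation under the null (6,000 runs, Monte Carlo standard error about 0.3 percentage points) gave 4.5%, so the planned test behaves about as stated.

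**Formula.** Let σe² be the residual variance and σc² the caregiver-by-wave variance. For the T2–T0 contrast, the true variance of the difference between arms is 4(σe² + mσc²)/n. An intercept-only model uses 4(σe² + σc²)/n. The ratio is 1 + (m − 1)ρ, with ρ = σc²/(σe² + σc²). Type I error is then 2[1 − Φ(1.96/√ratio)]. A ward-by-wave variance enters in the same way with m = 15.

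| Assumed setting | Ratio | Formula | Simulation |
|---|---|---|---|
| Stable caregiver error 0.1–0.2, m = 3–5, same rater | 1 | 5.0% | 5.1–5.2% |
| m = 1, σc² = 0.1 | 1 | 5.0% | 5.0% |
| m = 3, σc² = 0.05, σe² = 0.35 | 1 + 2 × 0.125 = 1.25 | 8.0% | 8.6% |
| m = 3, σc² = 0.1, σe² = 0.35 | 1 + 2 × 0.222 = 1.444 | 10.3% | 10.8% |
| m = 5, σc² = 0.1, σe² = 0.35 | 1 + 4 × 0.222 = 1.889 | 15.4% | 15.3% |
| 20% of raters replaced per interval, caregiver variance 0.1–0.2, m = 3 | – | – | 8.3–9.5% |
| Same, caregiver variance 0.2, m = 5 | – | – | 14.3% |
| Ward-by-wave 0.02, no caregiver error, σe² = 0.38 | 1 + 14 × 0.05 = 1.7 | 13.3% | 13.3% |

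In all these settings a comparison of follow-up levels, tested with the ward intercept, stayed at about 5%.

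**Which added term helps?**

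- *A caregiver intercept constant over time: no.* In four REML fits (3 clients per caregiver, same rater throughout), two of them with caregiver-by-wave error, adding it left the T2 interaction estimate and its standard error identical (for example −0.0328, SE 0.0916, both ways).
- *A caregiver-by-wave effect: yes, for the caregiver part.* With σe² = 0.4, rejection fell from 7.2% to 4.5% (m = 3, σc² = 0.05), from 9.7% to 4.7% (m = 3, σc² = 0.1) and from 13.8% to 4.6% (m = 5, σc² = 0.1).
- *It is not enough if wards also move.* Take m = 3, σc² = 0.05, σe² = 0.4 and ward-by-wave variance 0.02. A caregiver-level test then understates the variance by (0.4 + 3 × 0.05 + 15 × 0.02)/(0.4 + 3 × 0.05 + 3 × 0.02) = 0.85/0.61 = 1.393. The formula gives 9.7% and simulation 9.6%. Testing change against ward-level variation gave 5.1%.

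**The case against.** A reader might infer that leaving out the caregiver level is enough to make the client tests reject too often. The documents do not support that. Treatment is assigned by ward or location, caregivers sit within that unit, and ward is a random effect. Rater error that is stable over time cancels from change.

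Nor does the protocol say that caregivers rate several clients; it only allows for it. Equal totals of 330 would average about one client per nurse, although that is an enrolment target and not a rater assignment. The 20% is a sample-size allowance for losing nurses, not a stated rate at which clients change rater. It makes rater change plausible and does not measure it.

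The strongest objection is that the article never says the random effects are intercepts only, and a covariance structure is commonly left to the analysis plan. A ward-level random time effect would also absorb caregiver-by-wave error: tests at ward level gave 5.2–5.4% with no caregiver term at all. This stands in part. It makes the finding conditional and shows that the randomised unit is the level to secure first. It does not remove the point, because the article fixes both the list of random effects and the number of levels, and neither contains a time-varying cluster term.

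A further tempting inference is that the cost and QALY results suffer in the same way. They are 6-month totals with one record per client, so a caregiver-by-wave effect is not defined there, and a ward intercept would cover rater error nested within wards.

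**Conclusion.** The concern holds in conditional form. On the natural, intercept-only reading, the treatment-by-time test has no protection against shared errors that change between waves.

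Inflation from caregivers needs two things together: several clients per caregiver, and shared error that varies over time through drift or rater replacement. With 3 to 5 clients and the variances assumed here, type I error is about 8–15%; without either condition it stays at about 5%. Inflation from wards needs neither. A ward-by-wave variance of 0.02 is enough for about 13%, and on the same reading this applies to the nurse model as well.

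The true size cannot be determined from the protocol. It can be estimated from the trial's data only if the completing caregiver is recorded.

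**What to change.** 1. Store an identifier of the completing caregiver with every client questionnaire at every wave. The questionnaires are digital, so the burden is small. If it is not recorded, the caregiver component cannot be checked later.
2. State the random effects in full. In the client model, add a ward-by-wave random effect (location-by-wave where locations are randomised), and a caregiver-by-wave random effect where caregivers rate several clients.
3. Add the ward-by-wave term to the nurse model too.
4. In the economic regressions of 6-month totals, always include the randomised unit's random intercept instead of leaving it to judgement. No caregiver-by-wave term belongs there.

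The cost is one or two more variance components to estimate with 22 wards, and somewhat wider confidence intervals. For example, if change is tested at ward level on 22 − 2 = 20 degrees of freedom, the critical value rises from 1.96 to 2.086. That alone widens intervals by about 6% (2.086/1.96 = 1.064), even where no time-varying cluster variance exists.

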#### Economic evaluation

The economic evaluation will evaluate the cost-effectiveness of the SELF-program compared with care as usual over 6 months. The principal analysis will be the incremental cost per quality adjusted life year gained from the societal perspective using the EQ-5D-5L to calculate QALYs as recommended by the Dutch Healthcare Institute [45]. This will be calculated as the mean cost difference between the SELF-program and care as usual divided by the mean QALY difference to give the incremental cost-effectiveness ratio (ICER). Use of QALYs as a generic health outcome measure allows policymakers to compare cost-effectiveness results across different sectors to guide resource allocation decisions. Unit costs will be taken from the Dutch Manual for Costing in Economic Evaluations [49] and other standard published sources. The cost of the SELF-program will also include the costs related to the external actor, who is hired to guide the role-play session.

Estimates for mean total costs and QALYs’ incremental between the SELF-program compared with care as usual over 6 months will be derived using regression analysis to control for differences in baseline utilities and costs, as well as relevant stratification variables. A secondary analysis will include the cost per point change in the primary outcome measure (GARS-4) gained of the SELF-program compared with care as usual over 6 months. Where necessary, analyses will take into account clustering at the nursing home care level via random intercept models. Regression analysis will also be used in the secondary cost-effectiveness analysis to control for potential imbalances in baseline GARS-4 values and stratification variables. To quantify uncertainty around cost-effectiveness results, non-parametric bootstrap methods will be used and 95% bias-corrected and accelerated bootstrap confidence intervals will be calculated for the mean total cost and QALY/GARS-4 incremental estimates. The bootstrap replications will also be used to construct cost-effectiveness planes and cost-effectiveness acceptability curves, from which the probability that SELF-program is cost-effective compared to care as usual at 6 months of the trial will be computed for a range of values of the willingness to pay thresholds based on current recommendations [45].

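### The effect is read from change since T0, which is not the comparison the trial was sized for and is less precise than an analysis that adjusts for or constrains T0

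*Protocol article*

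**What the plan says.** **Sizing.** The protocol article (Sample size calculation) describes the anticipated benefit of the intervention in these words: "expected to induce a difference in groups’ averages of the primary outcome (the MAINtAIN-score), corresponding to a small to medium effect size of 0.4". This target is a standardized mean difference. The number of wards follows from a conventional comparison of means: "Using the two-tailed t-test, with power and significance level of 80% and 5%, respectively, the required number of clusters (K) was then computed". The other inputs are 15 nurses per ward, an intraclass correlation (ICC) of 0.05, 10% more clusters for unequal sizes and 20% attrition. No correlation between T0 and T1 scores is given.

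**Analysis.** Data analyses, Effect evaluation, describes a three-level mixed model with measurements nested in individuals and individuals in wards. Its fixed effects are: "Treatment, time and, their interaction, capturing treatment vs. control average differences over time, will make up the relevant fixed-effects". The only covariates named are background characteristics. The treatment-by-time coefficient on the standardized outcome is read as Cohen's d. MAINtAIN is measured at T0, 3 months and 9 months.

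**Economic evaluation.** For the client outcome this section takes another route: "Regression analysis will also be used in the secondary cost-effectiveness analysis to control for potential imbalances in baseline GARS-4 values and stratification variables".

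**The concern.** Treatment has its own main effect and T0 is one of the repeated measurements, so the arm means at T0 are free to differ. With T0 as the reference visit, the interaction is then the difference between arms in change from T0. Its variance depends on the T0–T1 correlation, which the sizing formula does not contain. The stated 80% power therefore belongs to a different comparison from the one to be tested.

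Precision is also at stake. A change contrast subtracts the whole T0 difference between arms. With about 11 wards per arm, chance differences at T0 are likely, and change carries them into the estimate at full weight. Adjusting for T0, or constraining the arms to a common T0 mean, gives T0 only the weight that its correlation with follow-up supports.

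**Working it through.** **Inputs from the protocol article:** d = 0.4 (SD 1), ICC 0.05, 15 nurses per ward, two-sided 5%, 80% power, +10% clusters, 20% attrition, 11 wards per arm.

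**Assumptions, not in the document:** nurse-level T0–T1 correlation ρ, varied from 0.2 to 0.5; a ward effect that is stable over time; time as categories with T1 against T0 as the contrast; pair-matching ignored.

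**1. The plan's own figure.** Nurses per arm without clustering: 2(1.96 + 0.84)²/0.4² ≈ 98.1. Design effect: 1 + 14 × 0.05 = 1.70. Then 98.1 × 1.70 = 166.8 per arm, and 166.8/15 = 11.1 wards per arm before any inflation. The stated K of about 8 does not reproduce. The later step does: 8 × 1.1/0.8 = 11 per arm, or 22 wards and 330 nurses. So 330 contains no real allowance for attrition or unequal clusters. That is a separate problem, but it sets the starting point here.

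**2. Power of the sizing t-test after attrition.** Completers per ward: 15 × 0.8 = 12. Effective wards per arm: 11/1.1 = 10. Variance of a ward mean: v = 0.05 + 0.95/12 = 0.129. SE = √(2 × 0.129/10) = 0.161, which gives 65% power (noncentral t, 18 df). With 11 wards the result is 70% (t, 20 df) or 74% (normal approximation).

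**3. The two ways of using T0.** Let r be the T0–T1 correlation of the *ward mean*. With a stable ward effect, r = [0.05 + (ρ − 0.05)/12]/0.129. The variance factor f relative to the t-test is:
- change from T0: f = 2(1 − r)
- adjusted or constrained for T0: f = 1 − r²

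The ratio of adjusted to change variance is (1 + r)/2, which is below 1 for every r below 1.

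**4. Results.** SE = √(2 × 0.129 × f/10), t with 18 df for both analyses. Example at ρ = 0.3: r = 0.0708/0.129 = 0.548. Change has f = 0.903 and SE 0.153. Adjusted has f = 0.699 and SE 0.134.

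| ρ (nurse) | r (ward mean) | f change | f adjusted | Power, change | Power, adjusted |
|---|---|---|---|---|---|
| 0.2 | 0.484 | 1.032 | 0.766 | 64% | 77% |
| 0.3 | 0.548 | 0.903 | 0.699 | 70% | 80% |
| 0.4 | 0.613 | 0.774 | 0.624 | 76% | 85% |
| 0.5 | 0.677 | 0.645 | 0.541 | 83% | 89% |

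The slope for T0 is treated as known, so the small cost of estimating it is ignored. With 11 wards and the normal approximation for both, ρ = 0.3 gives 78% against 88%.

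**5. Where change meets the two benchmarks.** Change equals the t-test at r = 0.5, which is ρ = 0.225 here, and beats it above that. Change reaches 80% after attrition at these values of ρ:
- about 0.45 under the table's assumptions
- about 0.33 with 11 wards and the normal approximation
- about 0.57 if change scores keep an ICC of 0.05 (11 wards, normal approximation)

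**The case against.** **A reader might infer that the choice of change leaves the trial below 80% unless the T0–T1 correlation is high.** The documents do not support this. The sizing t-test is already at 65 to 74% after attrition, before any change score enters. The stable ward effect cancels from the change, and it puts a floor of 0.05/0.129 ≈ 0.39 under r at the lowest possible ρ of 0.05. The correlation needed for 80% is therefore moderate.

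**The change contrast is standard, and sizing on a simple comparison is common and often conservative.** Both points stand. The article states nothing false here. Whether the arms share a T0 mean is not said outright, and free means are only the natural reading of the listed terms. But the article does fix those terms and the coefficient to be interpreted, so this is not merely detail left to an analysis plan.

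**The gain assumes arms that are comparable at T0.** This stands as a limit. In the recruitment section for nurses, those already allocated receive the letter, consent and then complete baseline. If knowledge of allocation affects who consents, T0 differences could be systematic. Change and adjusted estimates would then differ in bias, and neither is safer in every case.

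**The economic evaluation is no contradiction.** Agreed. A trial effect and a cost-effectiveness ratio may use different estimators. It does show that baseline adjustment is already accepted for GARS-4.

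**Using T0 only as a covariate drops nurses with T0 alone.** True. Constraining the T0 means keeps them.

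**Conclusion.** The point holds as one of efficiency and of matching the power statement to the analysis. The tested coefficient is, on its natural reading, a difference in change from T0. The trial was sized for a difference in group averages, and no T0–T1 correlation links the two. The planned contrast is valid, but it is less precise than a T0-adjusted or T0-constrained analysis at every correlation below 1.

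The loss is about 13 points of power at ρ = 0.2, falling to about 6 at ρ = 0.5. These figures rest on an assumed ρ, a stable ward effect, 12 completers per ward, 10 effective wards per arm, equal degrees of freedom for both analyses, and arms that differ at T0 only by chance. They do not show that the estimator causes the shortfall from 80%. That starts with the K of about 8 and the attrition allowance.

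**What to change.** **Effect evaluation.** Constrain the T0 arm means to be equal in the three-level model: keep time and the treatment-by-time terms at T1 and T2, and drop the treatment main effect at T0. Alternatively, take T1 and T2 as outcomes, with each nurse's T0 score and the ward-mean T0 score as covariates. Report the treatment difference at each follow-up visit. Use the same approach for GARS-4, in line with the baseline adjustment in the economic evaluation.

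**Sample size calculation.** Restate the power for that analysis over a stated range of T0–T1 correlation.

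**Sensitivity analysis.** Because consent and baseline follow allocation, also report the unconstrained change contrast.

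**Cost.** Revised wording, one repeated power calculation and one extra model per outcome. No new data are needed, since T0 is already collected. The covariate version loses nurses with T0 only; the constrained version does not.
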